### The intervention

EPIC-START combines validated data analytic tools with early nurse-initiated care protocols. The EPIC-START model of care incorporates three components: (i) EPIC, (ii) START, and (iii) a deterioration tool. An example of the clinical application of EPIC-START is presented in Fig. 2.

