**Fig. 2 Fig2:**
[figure not shown]
Example of the EPIC-START model of care in action

Emergency nurse Protocols Initiating Care (EPIC) is a clinical framework to support the early delivery of standardised evidence-based treatment by emergency nurses for the most common ED presentations. There are 73 EPIC protocols—41 adult and 32 paediatric—which were developed in 2021–2022 by the NSW Agency for Clinical Innovation (ACI) with clinician and policy stakeholders (see NSW Health website). All EPIC protocols are structured on the validated HIRAID™ emergency nursing framework (History, Identify Red flags, Assessment, Interventions, Diagnostics, communication and reassessment) [10]. The EPIC component of EPIC-START is planned for staged state-wide implementation in 2023.

The second component is the Sydney Triage to Admission Risk Tool (START), which is a validated decision support/risk assessment tool at the point of triage [14]. This tool combines the presenting health concern with various other data elements available at the point of triage to estimate the risk of hospital admission or discharge to support senior clinical decisions about streaming and disposition from ED. The START component has been piloted and evaluated in Sydney, NSW [9, 14].

The third element is a clinical deterioration tool that uses an alert system to support earlier detection of, and senior medical response to, patients at risk of clinical deterioration. The clinical deterioration alert system is based on the Modified Early Warning Score (MEWS) [15]. This validated tool estimates the risk of clinical deterioration resulting in death or intensive care unit admission based on vital sign observations routinely recorded by clinicians in the electronic medical record (eMR) observation charts with a reported AUROC of 0.83 (95% CI, 0.83–0.84) [16]. MEWS is one of many early warning scores available that was chosen because of its high sensitivity to the general ED population, and because it uses data that is routinely collected in Australian EDs. Other tools have items such as hypercapnic respiratory failure, which are not routinely collected [17].

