### Trial design

The *effectiveness-implementation hybrid design* [12] comprises a closed cohort stepped–wedge cluster randomised controlled trial supported with implementation frameworks to test the implementation strategy and the outcomes of the intervention. A stepped–wedge cluster randomised controlled trial design is considered appropriate for implementation evaluations of health service interventions as it simplifies data collection procedures, supports logistical processes better, aligns with ethical principles, accommodates temporal issues, and optimises financial constraints. The stepped–wedge cluster randomised controlled trial addresses the ethical dilemmas of randomised trial design where essential investigations and/or best-practice treatments may be withheld from control participants [12].

The closed cohort stepped–wedge, cluster randomised controlled trial design involves a sequential rollover of the intervention at four local health district clusters after baseline. This study will be conducted in four local health districts in NSW, Australia. Each cluster will begin in the control condition (baseline data collection) and will sequentially receive the intervention at 6-week intervals.

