### Statistical methods

For each outcome of interest, data collected across all measurement periods and all study data collection time points will be used to compare intervention status (pre versus post). Analyses will apply the intention-to-treat principle. Patient data will be analysed according to the status of the study EDs (i.e. pre- or post-intervention) where patients were presented and treated. Outcomes will be assessed at the patient level using mixed effect models, considering the correlation of patient presentation within ED and local health district (cluster) and multiple presentations for the same patient, with adjustment for potential confounding factors. For example, for ED LOS analysis, we will adjust for patient characteristics, e.g. age and gender and clinical characteristic, e.g. number of laboratory tests ordered. The mixed models will also incorporate fixed terms for intervention status and measurement time points (including baseline). The analyses will include multiple time points pre- and post-intervention. The study design will allow us to determine temporal changes in system effectiveness, e.g. if ED LOS continues to decrease over time.

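### The ED length-of-stay model adjusts for the laboratory test count, which accrues after exposure and can distort the total effect in H1

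*Protocol article*

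**What the plan says.** The Statistical methods section of the protocol plans patient-level mixed models "with adjustment for potential confounding factors". For ED LOS it gives age and gender as patient characteristics and a "clinical characteristic, e.g. number of laboratory tests ordered". The test count is introduced as an example, but the sentence states an intention to adjust, and this is the only clinical covariate named. The same section says: "Analyses will apply the intention-to-treat principle". It classifies patients by the pre- or post-intervention status of the ED they attended. It describes no LOS model without the count and no mediation analysis.

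H1, under Stage 4, is that LOS in ED becomes 1 h shorter as a result of implementation.

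Under The intervention, the protocol states: "EPIC-START combines validated data analytic tools with early nurse-initiated care protocols". EPIC itself is "a clinical framework to support the early delivery of standardised evidence-based treatment by emergency nurses", and all EPIC protocols are built on a nursing framework whose elements are "History, Identify Red flags, Assessment, Interventions, Diagnostics, communication and reassessment".

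**The concern.** A confounder must not be a consequence of exposure. Age and gender meet that condition. A count of tests ordered during the stay does not obviously do so, because it is settled only once the patient has been managed under one condition or the other.

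The count can be linked to exposure in two ways:

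- **Route A, mediation.** Protocols with a diagnostics element may lead to more tests or to fewer repeat tests. If tests take time, part of the effect on LOS runs through the count, and holding the count fixed removes that part. If unmeasured severity raises both tests and LOS, conditioning on the count also opens a path through severity.
- **Route B, dependence on the outcome.** A longer stay leaves more time for tests. A real reduction in LOS then lowers the count, and adjusting for it takes back part of the reduction.

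H1 is a total effect under intention to treat. A model conditioned on such a count answers a different question, roughly the effect on LOS among patients with the same number of tests.

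**Working it through.** **Inputs from the protocol.** The target effect is 1 h (H1). The SD is 5.4 h, the ICC 0.05 and the cell size 1420 per cluster and time point (Sample size). There are four clusters and four start dates after baseline (Trial design, Randomisation), taken here as 5 periods. The protocol gives no hours of LOS per test, no mean number of tests and no expected change in tests. So it has no figure of its own to reproduce on this point, and every magnitude below rests on assumptions.

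**Step 1: order of events.** Age, gender, triage category and presenting problem are known at or before triage. Tests are ordered after that, during the stay whose length is the outcome. The count is therefore recorded after exposure and overlaps in time with the outcome.

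**Step 2: route A without severity.** Let τ be the total effect, b the hours of LOS per test and d the change in mean tests caused by the intervention. The adjusted coefficient is

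adjusted = τ - b × d.

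Assume τ = -1 h and b = 0.5 h. The formula was compared with a simulated stepped wedge (4 clusters, 5 periods, 1420 per cell, about 2 tests per patient, fixed cluster and period terms):

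| Change in tests, d | Formula | Simulated, adjusted | Simulated, unadjusted |
|---|---|---|---|
| -0.5 | -1 + 0.25 = -0.75 h | -0.71 h | -0.96 h |
| 0 | -1.00 h | -0.99 h | -0.99 h |
| +0.5 | -1 - 0.25 = -1.25 h | -1.24 h | -1.00 h |
| +1.0 | -1 - 0.50 = -1.50 h | -1.53 h | -1.03 h |

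The small departures of the unadjusted column from -1 h are simulation noise.

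**Step 3: route A with unmeasured severity.** Add a severity factor that raises tests and also raises LOS by 1 h per SD (assumed).

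| Change in tests, d | Adjusted | Unadjusted | Difference |
|---|---|---|---|
| -0.5 | -0.62 h | -1.00 h | +0.38 h |
| 0 | -0.99 h | -0.98 h | -0.01 h |
| +0.5 | -1.34 h | -0.97 h | -0.37 h |
| +1.0 | -1.73 h | -0.98 h | -0.75 h |

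The distortion is now about 0.75 h per test (0.75 / 1.0) instead of 0.5 h, because the count partly stands in for severity. With no change in tests it is still nil.

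**Step 4: route B, not included in the simulation.** Suppose the only link between tests and LOS is that longer stays accumulate tests:

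LOS = τX + e, tests = c × LOS + u.

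The coefficient of tests in the adjusted model is β = c·var(e) / (c²·var(e) + var(u)). Hence

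adjusted = τ(1 - cβ) = τ(1 - r²),

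where r is the correlation of tests and LOS within condition. For assumed r = 0.3 this is -1 × (1 - 0.09) = -0.91 h. For r = 0.5 it is -1 × (1 - 0.25) = -0.75 h. The loss is 9% to 25% of the effect, although the intervention has no direct influence on ordering.

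**Step 5: taken together.** Route A can move the estimate either way, depending on the sign of d. Route B alone moves it toward zero. The documents do not say which operates, so the net sign cannot be stated.

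**The case against.** The strongest reply is that the protocol nowhere says EPIC-START changes the number of tests. It speaks of early care, which concerns timing and who starts it. The same tests ordered sooner leave the count as it was, and Steps 2 and 3 show nil distortion in that case. The diagnostics element comes from expanding the name of the nursing framework, training in that framework is a prerequisite to EPIC training, and the education is meant to build on what nurses already do. How much diagnostic activity is new is not stated. In addition, the four clusters differ widely (Table 1), so adjusting for case complexity is a legitimate aim.

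Much of this stands, and it limits the point. Several stronger readings should not be drawn:

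- A reader might infer that the H1 estimate is biased. The documents support only that it can be.
- A reader might infer that the ICER inherits the problem. The Cost-effectiveness section refers to relevant confounders and does not name the test count. The ICER is affected only if the same covariate or the test-adjusted LOS effect is carried into it.
- A reader might infer that every effect model is affected. The count is named only for ED LOS.
- A reader might take the remark in Trial design that "essential investigations and/or best-practice treatments may be withheld from control participants" as describing this trial's control condition. It is a general ethical argument about randomised designs and carries no weight here.
- A reader might multiply assumed hours per test by an assumed shift in tests and report a percentage of the 1 h target. Any such range must include zero and leaves out route B.

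The reply does not rescue the covariate. Unchanged timing-only ordering answers route A but not route B. If neither route operates, the count is not needed to remove bias. The wish to adjust for case mix can be met with information available at triage.

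**Conclusion.** The point holds in a limited form. The LOS model names as a confounder a variable that is determined after exposure, that the intervention may change and that LOS itself may drive. Conditioning on it can move the estimate away from the intention-to-treat total effect that H1 describes.

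The structural point is firm and needs no assumption about size. Size and direction are unknown. In the assumed cases above, a true -1 h appeared as anything from -0.62 h to -1.73 h, and as -1 h apart from simulation noise when test numbers did not shift and did not depend on LOS. These figures show that the issue could matter against a 1 h target; they do not estimate what will happen in this trial. The matter is worth settling before results are seen, because it decides what the H1 coefficient means.

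**What to change.** In Statistical methods, remove the laboratory test count from the primary H1 LOS model. State that adjustment is limited to characteristics recorded at or before triage, for example age, gender, triage category and presenting problem. Since ED staff record the last two at triage, where START also operates, the sponsor should confirm that their recording does not change with the intervention.

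Report tests ordered as a process outcome by condition, or use the count in an analysis labelled as mediation or sensitivity. State in Cost-effectiveness that the LOS effect used for the ICER is not the test-adjusted one.

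The cost is a sentence or two of text and possibly slightly less explained variance. No stated sample size changes, and the replacement covariates are of a kind already recorded at triage.

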#### Stage 3: Implement EPIC-START

Implementation of the EPIC-START model of care will occur sequentially at the clusters to ensure geographically and clinically diverse ED settings using the strategies identified as effective in stage 2. These strategies will be applied consistently to ensure implementation fidelity*.*

Ongoing implementation support strategies will continue during the implementation stage: for example, the staff at each site will continue to receive support and coaching from the implementation team and updates on the implementation efforts. An implementation nurse will manage each cluster funded by the study. Following implementation, EPIC-START will become part of routine mandatory training to ensure sustainability.

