### Methodological considerations and risks

There are foreseeable risks to the implementation and evaluation of EPIC-START in this study, such as changes to the electronic medical record systems, COVID-19 and natural disasters, and competing projects, for which mitigation strategies have been established. Partner agreements were obtained as part of the study proposal/design and co-design of implementation strategies with clinicians and service leaders to reduce risk. Other risks may be delays in the publication of EPICs, integration and uptake of the SMART, and deterioration tools into eMR and clinician practice.

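### A single pre/post term assumes a full and constant effect from crossover, so it would underestimate an ED length-of-stay effect that builds up, which the same section sets out to examine

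*Protocol article*

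**What the plan says.** The Statistical methods section pools all measurement periods, and the data "will be used to compare intervention status (pre versus post"). Patients are classed by the state of the ED they attended: "Patient data will be analysed according to the status of the study EDs (i.e. pre- or post-intervention"). On the model it says: "The mixed models will also incorporate fixed terms for intervention status and measurement time points (including baseline"). It mentions no term for time since crossover, no interaction of status with exposure time and no transition period.

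The same paragraph ends with an aim about change over time: "The study design will allow us to determine temporal changes in system effectiveness, e.g. if ED LOS continues to decrease over time".

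Two other places bear on how fast an effect might appear. Under Stage 3, "staff at each site will continue to receive support and coaching from the implementation team" during implementation. Under Methodological considerations and risks, the article writes: "Other risks may be delays in the publication of EPICs, integration and uptake of the SMART, and deterioration tools into eMR and clinician practice".

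The Trial design section has four local health district (LHD) clusters crossing over one after another at 6-week intervals after baseline. The number of measurement periods is not given.

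**The concern.** In a stepped wedge with fixed period effects, a 0/1 status term is not a simple average of the effect over time since crossover. LHDs that crossed early serve as comparators for those that cross later. If the effect in the early LHDs is still growing, the period terms absorb part of that growth and it is subtracted from the estimate. Effects at long exposure can then carry negative weight.

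Hypothesis H1 is a 1-h reduction in ED LOS, and the Cost-effectiveness section expresses its ratio per hour of LOS prevented. A programme that takes a step or two to bed in could therefore look much weaker than it is. This is bias from the model, so large patient numbers do not remove it. In addition, the terms named do not by themselves answer the question about a continuing fall in LOS: the status term is constant, and the time-point terms represent calendar trend common to all LHDs.

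**Working it through.** **Inputs.** From the Trial design section: four LHDs, one per 6-week step, after baseline. From the Sample size section: SD 5.4 h, ICC 0.05, 1420 presentations per LHD per time point, target 1 h. Assumptions of this review: one baseline period (5 periods in all), varied below, and cluster autocorrelation (CAC) of 1, varied below.

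**The plan's own figure.** The plan gives no figure for this point. Its 1420 is used only as an input. A standard stepped-wedge design-effect calculation with the stated inputs gives about 145 per LHD per time point, so 1420 is not reproduced. With an unstated CAC of 0.8 to 0.9, 1420 gives 61% to 86% power for 1 h, so it cannot be called wrong. The weights below hardly depend on it.

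**Weights.** Let X = 1 after crossover and 0 before. With LHD and period effects removed, each cell contributes r = X - (LHD mean of X) - (period mean of X) + 0.5. The LHD means are 0.8, 0.6, 0.4 and 0.2. The period means are 0, 0.25, 0.5, 0.75 and 1. For the post-crossover cells:

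- LHD 1: 0.45, 0.20, -0.05, -0.30
- LHD 2: 0.40, 0.15, -0.10
- LHD 3: 0.35, 0.10
- LHD 4: 0.30

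Sums by exposure period:

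- Period 1: 0.45 + 0.40 + 0.35 + 0.30 = 1.50
- Period 2: 0.20 + 0.15 + 0.10 = 0.45
- Period 3: -0.05 - 0.10 = -0.15
- Period 4: -0.30

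The total is 1.50. Dividing by it gives weights 1.0, 0.3, -0.1 and -0.2. Exact generalised least squares with a random LHD effect, 1420 per cell and ICC 0.05 gives 0.998, 0.300, -0.099 and -0.199. The weights barely move for ICC 0.01 to 0.18 or CAC 0.8 to 1. With two baseline periods they are 0.90, 0.30, -0.05 and -0.15. With four they are 0.80, 0.30, 0.00 and -0.10.

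**Expected estimates.** Each is the weighted sum of the assumed LOS reductions (h). For linear growth: 0.998×0.25 + 0.300×0.5 - 0.099×0.75 - 0.199×1.0 = 0.13.

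| Reduction in exposure periods 1 to 4 | True average | 1 baseline | 2 baseline | 4 baseline |
|---|---|---|---|---|
| 0.8, 1, 1, 1 | 0.95 | 0.80 | 0.82 | 0.84 |
| 0.5, 1, 1, 1 | 0.88 | 0.50 | 0.55 | 0.60 |
| 0.25, 0.5, 0.75, 1 | 0.63 | 0.13 | 0.19 | 0.25 |
| 0, 1, 1, 1 | 0.75 | 0.00 | 0.10 | 0.20 |
| 0, 0.5, 1, 1 | 0.63 | -0.15 | -0.05 | 0.05 |
| 0, 0, 1, 1 | 0.50 | -0.30 | -0.20 | -0.10 |

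With ED-level as well as LHD random effects, and 11, 3, 4 and 12 sites in any order, linear growth gives 0.09 to 0.17 h (one baseline period).

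**Alternative model.** One indicator per exposure period, averaged, recovers the true average for any of these curves. At 1420 per cell its SE is 0.183 h against 0.114 h for the single term, a ratio of 1.6 (variance ratio about 2.6). With CAC 0.9 the SEs are 0.52 and 0.33 h.

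**The case against.** A reader might infer that the plan expects a gradual effect. It does not say so. The continuing fall in LOS is given as an example of something to be examined, delayed uptake is listed as a risk, and continued coaching does not imply that the effect grows. Stage 3 also says the strategies will be applied consistently. If most of the effect is present in the first 6 weeks, the attenuation is small.

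A reader might also infer that the single term will show harm where there is benefit. That is specific to the curve and the layout. The 0, 0.5, 1, 1 h example has the wrong sign with one or two baseline periods but not with four. Only a full two-step lag stays negative with four (-0.10 h). The number of periods is itself unclear: the Trial design section uses 6-week steps, while the Sample size section counts quarters (1920 / (4 × 120) = 4) and the analysis is to include several time points before and after. Attenuation, by contrast, appears in every layout tried.

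The article is condensed, its list of terms is not presented as complete, and an analysis plan that is not shown may add exposure-time terms. It therefore cannot be said that the aim on temporal change will go unmet. But the article does commit to a pre/post comparison with a named status term beside an aim which that term cannot serve. That conflict is in the text and is not merely missing detail.

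Finally, with four LHDs the alternative is costly. At about 19,000 presentations per cell (666,571 × 6/52 / 4 = 19,228) and CAC 0.9, the SE rises from 0.31 to 0.49 h, and power for a constant 1 h falls from 90% to 53%. This stands. It argues for reporting both models rather than replacing one with the other.

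**Conclusion.** The point holds as a conflict between the stated effect term and the stated aim, with a bias whose size depends on how fast the effect builds. Under one baseline period and four 6-week steps, linear growth to 1 h is estimated at 0.13 h against a true average of 0.63 h (0.19 to 0.25 h with two to four baseline periods). Half effect for 6 weeks and full effect afterwards gives 0.50 h against 0.88 h. A near-complete effect in the first step gives only modest attenuation (0.80 h against 0.95 h). A wrong sign needs a lag of nearly two steps together with few baseline periods, or a lag of two full steps. The conclusion rests on assumed effect curves and an assumed number of periods. It hardly depends on the ICC, the CAC or the number of patients.

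**What to change.** 1. Name the effect to be estimated, for example the average over a stated span of time since crossover, and state the number of measurement periods.
2. Pre-specify a second model with indicators for periods since crossover in place of the single status term. Report the pattern of the indicators as the answer on temporal change, and their average alongside the constant-effect estimate.
3. State that no conclusion of no effect or harm will be drawn from the single term if the exposure-time estimates are not constant.
4. Identify exposure-time effects only through the modelled comparison between LHDs at different exposure. In a layout of four LHDs and five periods, the fourth exposure period is seen only in the first LHD, in the last period. A continued fall in LOS in periods where every LHD has the same status should not be read as an intervention effect unless that assumption is stated.
5. Restate power for the averaged effect.

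The change needs analysis wording and no new data. Its price is precision: an SE about 1.6 times larger (0.114 to 0.183 h at 1420 per cell with CAC 1; 0.33 to 0.52 h with CAC 0.9). For an average effect of 0.625 h at 1420 per cell, power is about 93% with CAC 1 and about 36% with CAC 0.95. The CAC is not in the article and should be given as an assumption with a range.
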